#### Statistical Analysis

Descriptive statistics will report continuous data as mean (SD) for normally distributed variables and categorical data as frequency and percentage (N, %). Feasibility metrics and T1D stages will also be summarized as percentages.

To evaluate the psychological effects of T1D screening on caregivers, pre- and postscreening levels of anxiety, depression, and distress will be compared using paired 2-tailed *t* tests or Wilcoxon signed-rank tests, depending on data distribution. The effectiveness of educational counseling will be analyzed similarly, comparing pre- and postintervention test scores. Longitudinal changes in the psychological measures will be evaluated using repeated-measures ANOVA or mixed effects models to track patterns over time.

For participants with presymptomatic T1D, progression rates to stage 3 will be analyzed using Kaplan-Meier survival analysis. Time to event will be calculated from screening age to age at stage-3 T1D diagnosis or last follow-up. Cox proportional hazards models will assess factors associated with disease progression, such as baseline autoantibody titers, genetic risk scores, and demographic variables.

At the 1-year follow-up, cost-effectiveness will be assessed by reporting total costs for all screened participants, cost per child screened, and cost per case detected. The incremental cost-effectiveness ratio calculations will compare outcomes for screened children with controls diagnosed with stage-3 T1D in the general population. The incremental cost-effectiveness ratio will incorporate potential benefits, such as reduced DKA incidence and improved HbA_1c_ levels, while adjusting for control characteristics like age and FDR status.

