##### Participants With Positive Results

Families of participants who test positive for multiple islet autoantibodies are invited to a one-to-one counseling visit with a research physician to discuss the result, followed by a group education and metabolic staging to determine their T1D stage.

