##### Participants With Equivocal Results

Families of participants with a single autoantibody are invited for a one-to-one counseling session with a physician to discuss the result. They then join the same group educational session as those with positive results.

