#### Educational Curriculum for Participants With Positive or Equivocal Results

The educational curriculum was developed based on a comprehensive robust educational framework and expertise [51]. It is delivered in small group sessions by experienced endocrinologists, diabetes educators, and dietitians. The curriculum covers key topics such as T1D pathophysiology, disease progression stages, and the importance of early detection. Participants learn to identify their specific stage and risk of progression and recognize factors that influence clinical diabetes onset. The curriculum highlights insulin’s role as the primary treatment for clinical T1D (stage 3), addressing common concerns and misconceptions. Participants are also trained to monitor their condition by recognizing early T1D symptoms, performing blood glucose checks, interpreting results, and determining when insulin therapy or medical advice is needed.

The program underscores nonpharmacological strategies for reducing the risk of T1D progression through healthy eating and lifestyle modifications and provides an overview of current and future T1D research. The psychological and emotional aspects of receiving T1D screening results are also addressed, and access to support is provided.

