#### Effectiveness of Educational Interventions

The effectiveness of the educational curriculum will be evaluated using pre- and postintervention tests completed by caregivers. These tests are developed to measure changes in knowledge related to the curriculum’s objectives, providing a comprehensive assessment of the intervention's effectiveness in preparing caregivers for presymptomatic T1D management.

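### The education outcome is tested with paired tests on individual caregivers although the curriculum is taught in shared small groups; if gains correlate within sessions, the uncertainty is understated

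*Protocol article*

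**What the plan says.** Under Effectiveness of Educational Interventions, the protocol article says that the curriculum's effect "will be evaluated using pre- and postintervention tests completed by caregivers". The unit of measurement is therefore the individual caregiver.

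Under Statistical Analysis, the method is given by reference: "The effectiveness of educational counseling will be analyzed similarly, comparing pre- and postintervention test scores". The sentence before it concerns the psychological measures. It names a two-sided paired t test and offers a rank-based alternative, in the words "tests or Wilcoxon signed-rank tests, depending on data distribution". The test for the education outcome is thus a paired t test or its rank-based counterpart, on one pre/post pair per caregiver.

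The delivery is described under Educational Curriculum for Participants With Positive or Equivocal Results: "It is delivered in small group sessions by experienced endocrinologists, diabetes educators, and dietitians". For families of children with multiple autoantibodies, the one-to-one visit is "followed by a group education and metabolic staging to determine their T1D stage". Of families with a single autoantibody, the article says: "They then join the same group educational session as those with positive results".

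Mixed effects models appear only for another outcome: "Longitudinal changes in the psychological measures will be evaluated using repeated-measures ANOVA or mixed effects models". For the knowledge scores, the article names no session or family term and no cluster-robust standard error.

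**The concern.** Both named tests take the caregivers' change scores to be independent of each other. Caregivers who sit in one session share its delivery and discussion, so a session that goes well or badly tends to move all of its members' gains together. Pairing does not remove this. It takes out stable differences between caregivers in their level of knowledge, but a session effect acts on the gain itself, which is the quantity being estimated.

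The clustering arises from how the intervention is delivered, so it can be present even with one caregiver per family. Two caregivers from one family would add a second level.

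At stake is the stated precision of the education effect, which is a named secondary objective. The pilot is also meant to inform a national programme. How much the gain varies from session to session is useful for that purpose, and the planned test does not show it.

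**Working it through.** **No stated figure to reproduce.** The article gives no sample size, power, expected gain, SD, session size or ICC for the education comparison. The target of 1300 participants in 322 families does not concern it.

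**Inputs**
- From the article (Sample Size): 1300 participants and seropositivity of 5% to 15%, so 1300 × 0.05 = 65 to 1300 × 0.15 = 195 antibody-positive children.
- Assumed: about one caregiver tested per positive child, session size m of 5 to 10, and ICC of the change score of 0 to 0.20.

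**Formulas**
- Design effect: DE = 1 + (m − 1) × ICC.
- Shortfall of the paired-test standard error: 1 − 1/√DE.
- Effective sample size: n/DE.

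**Results**

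| m | ICC | DE | SE too small by |
|---|---|---|---|
| any | 0 | 1.00 | 0% |
| 5 | 0.01 | 1 + 4 × 0.01 = 1.04 | 2% |
| 10 | 0.01 | 1 + 9 × 0.01 = 1.09 | 4% |
| 5 | 0.05 | 1 + 4 × 0.05 = 1.20 | 9% |
| 8 | 0.05 | 1 + 7 × 0.05 = 1.35 | 14% |
| 8 | 0.10 | 1 + 7 × 0.10 = 1.70 | 23% |
| 10 | 0.20 | 1 + 9 × 0.20 = 2.80 | 40% |

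At m = 8 and ICC 0.05, 65 caregivers carry the information of 65/1.35 ≈ 48 independent ones, and 195 that of 195/1.35 ≈ 144.

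**Check by simulation: type I error.** Change scores with a shared session component and no true gain were generated in sessions of 8, with 20,000 data sets per setting. The table gives the rejection rate of a nominal two-sided 5% test.

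| Sessions of 8 | ICC | Paired t on caregivers | t on session means |
|---|---|---|---|
| 8 | 0 | 5.0% | 5.1% |
| 8 | 0.05 | 9.2% | 5.1% |
| 8 | 0.10 | 13.2% | 5.2% |
| 8 | 0.20 | 20.8% | 5.1% |
| 24 | 0.05 | 9.3% | 5.1% |
| 24 | 0.20 | 20.9% | 4.9% |

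More sessions of the same size do not cure the inflation. The session-level test holds its level.

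**Check by simulation: coverage.** With 10 sessions of 8, the nominal 95% paired-t interval covered the true gain in 90.7%, 86.4% and 79.2% of data sets at ICC 0.05, 0.10 and 0.20.

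**The case against.** - **The size is assumed throughout.** This stands. Neither session size nor ICC is in the article. At ICC 0.01 the effect is negligible, and at zero there is none. The documents support saying that the standard error may be too small. They do not support saying that it will be.
- **The source of correlation is partly inferred.** This stands in part. The article describes one curriculum, and participants are recruited from one centre. If one team teaches every session, the instructors are a constant and do not create correlation within sessions. Shared discussion and session-to-session variation in delivery remain.
- **The decision would rarely change.** This largely stands. The outcome is an uncontrolled pre/post comparison with no threshold attached. In simulations of 10 sessions of 8 with a mean gain of 0.8 SD of the change score, the paired test rejected in at least 99.9% of runs and a session-level test in at least 98%, at every ICC from 0.01 to 0.20. They parted clearly only for a moderate gain with a high ICC: 94% against 73% at 0.5 SD and ICC 0.20.
- **The detail belongs in an analysis plan that is not shown.** This limits the point but does not remove it. The random-effect structure and the degrees of freedom can be left to that plan. The article nevertheless names the tests, and as named they assume independence.

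A reader might go further and infer that the number of independent units is closer to the number of sessions than to the number of caregivers. The arithmetic does not bear this out in general. With 10 sessions of 8, the 80 caregivers are worth 80/1.35 ≈ 59 at ICC 0.05, 80/1.70 ≈ 47 at 0.10 and 80/2.40 ≈ 33 at 0.20. The midpoint between 10 and 80 is 45, so the statement is true only at the highest of these.

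A reader might also infer that modelling session would let the result carry over to other educators. It would not: a session is not an educator, and no educators outside the programme are sampled.

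**Conclusion.** The point holds in a limited form. The article names tests that need independent gains and describes a delivery that gives reason to doubt that independence. Nothing else in it repairs this for the knowledge scores.

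The direction rests on a positive within-session correlation, which is usual for shared teaching but is not shown here. For assumed sessions of 5 to 10, the effect runs from none at ICC 0, through negligible at 0.01, to a standard error 9% to 40% too small at 0.05 to 0.20. The consequence is mainly understated uncertainty on a secondary, uncontrolled outcome. It would be too strong to infer that a finding of effective education is likely to be wrong, because a large gain would probably stay significant.

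The change is worth making because it is cheap and because the session identifier may not be recoverable later.

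**What to change.** Record a session identifier and a family identifier with every pre and post test. In the Statistical Analysis section, replace the reference to the paired tests for the education outcome with wording such as:

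*The change in knowledge score will be analysed with a linear mixed model with a random intercept for session, and for family where two caregivers attend, using Kenward-Roger or Satterthwaite degrees of freedom. The mean gain will be reported with its 95% confidence interval.*

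A one-sample t analysis of session mean gains is a simple alternative.

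The cost is two identifiers on the test form, one sentence of analysis text and a somewhat wider interval. If the ICC proves close to zero, little precision is lost. The programme began in May 2024, so for any session already held the identifier has to be recovered from session dates, which works only if those dates were kept.

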#### Secondary Objectives

The secondary objectives are as follows:

Examine the psychological impacts of T1D screening on caregivers, including changes in anxiety, depression, distress level, and health-related quality of life before and after receiving screening results.Evaluate the effect of early detection on reducing DKA incidence at stage-3 T1D onset.Analyze the cost-effectiveness of implementing a T1D-screening program in Saudi Arabia.Evaluate the natural history of T1D progression in identified presymptomatic individuals, tracking time to clinical onset and changes in health outcomes over time.Examine the effectiveness of educational interventions on caregivers’ knowledge of T1D screening and early identification.Investigate the genetic predisposition to T1D within our population through human leukocyte antigen (HLA) testing and validate the genetic risk score (GRS) 2 in the Saudi population.

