#### Informed Consent

Eligible families are scheduled for T1D-screening visits, where informed consent and assent are obtained. A comprehensive educational approach was developed to ensure participants receive standardized information and fully understand the T1D-screening process. This included an animated video and an educational booklet. The video, in Arabic, explains the screening program and key concepts, such as T1D pathophysiology, its stages, and clinical presentation. It emphasizes the benefits of early detection in preventing DKA and improving long-term outcomes; outlines the screening process; and provides an overview of current and emerging T1D treatments, including insulin therapy and disease-modifying interventions. The educational booklet complemented the video, using infographics to illustrate T1D pathophysiology, stages, symptoms, and benefits of screening. It also outlined study expectations and provided key study contact information.

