### Phase 3: Long-Term Monitoring and Clinical Follow-Up

#### Monitoring for Disease Progression

Participants with positive single or multiple autoantibodies will enter a 4-year follow-up phase. During this period, regular assessments are performed to monitor T1D disease progression, track time to clinical onset, and observe any changes in metabolic staging. Monitoring intervals vary by stage and risk level [18,20]. Participants progressing to stage-3 T1D will transition to standard care.

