## Discussion

The VISION-T1D protocol outlines a comprehensive approach to assess the feasibility and impact of a T1D screening among FDRs of individuals with T1D in Saudi Arabia. This model is tailored to address the unique demographic, cultural, and health care characteristics of the Arab region, aiming to deepen understanding of the prevalence and patterns of autoimmunity in at-risk populations. The data generated will provide valuable epidemiological insights to inform future health care policies and targeted interventions.

A key strength of this study is its focus on translating screening programs from the research setting to practical, real-world implementation. It provides a detailed roadmap for integrating T1D screening into health care systems, addressing scientific and operational complexities, particularly within the Arab region. The use of culturally sensitive consent materials, diverse educational methods, and clear protocols ensures that participants and caregivers are well informed, supported, and empowered to manage their health proactively. Additionally, the adoption of the ADAP assay—a cost-effective, sensitive, and low-sample-volume technology—enhances scalability and operational efficiency, making the program accessible for large-scale applications.

This study addresses significant unmet needs in T1D care and research in the Middle East, offering critical insights into genetic predispositions and disease progression in the Saudi population. One of the program’s pivotal contributions is the early identification of candidates for T1D prevention therapies. Early detection through screening will facilitate timely intervention with disease-modifying therapies that can delay or prevent the onset of clinical T1D. This proactive approach aligns with global health strategies advocating for prevention and early intervention to mitigate the long-term burden of chronic diseases. Furthermore, this initiative lays the groundwork for the future of prevention trials in Saudi Arabia, contributing to the development of a sustainable infrastructure for T1D research and management.

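### If any child starts a disease-modifying therapy, the progression rule counts treated time as natural history

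*Protocol article*

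**What the plan says.** The relevant text of the protocol article is in five places.

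- **Secondary Objectives:** "Evaluate the natural history of T1D progression in identified presymptomatic individuals, tracking time to clinical onset and changes in health outcomes over time".
- **Statistical Analysis, estimator and time rule:** for children with presymptomatic disease, "progression rates to stage 3 will be analyzed using Kaplan-Meier survival analysis". The next sentence fixes the time axis: "Time to event will be calculated from screening age to age at stage-3 T1D diagnosis or last follow-up".
- **Statistical Analysis, regression:** "Cox proportional hazards models will assess factors associated with disease progression, such as baseline autoantibody titers, genetic risk scores, and demographic variables". No therapy term is among the examples, but the list is open.
- **Discussion:** "Early detection through screening will facilitate timely intervention with disease-modifying therapies that can delay or prevent the onset of clinical T1D". The same paragraph counts finding candidates for prevention therapies among the programme's main contributions.
- **Informed Consent:** the video shown to families "provides an overview of current and emerging T1D treatments, including insulin therapy and disease-modifying interventions".

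Follow-up lasts four years (Monitoring for Disease Progression), and progression is to be reported by initial stage (T1D Progression Rate). No section provides disease-modifying therapy as a study procedure, and none gives an expected uptake.

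**The concern.** Natural history ordinarily means the course without treatment that alters it. The time rule has two endpoints, stage 3 and last follow-up. A child who starts a delaying therapy in year one and is still free of stage 3 in year four therefore contributes four years of apparent natural history, most of them treated.

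The resulting figure is a legitimate one, progression under screening and whatever care follows, but it does not answer the objective as worded. The article says its results will inform a national programme and that the initiative lays groundwork for prevention trials. Anyone who takes the stage-specific rates as untreated rates for those purposes would start too low if some children had been treated. Start dates that are not collected as they occur may also be hard to recover later.

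**Working it through.** The article states no expected progression rate, event count or power for this analysis, so there is no figure of its own to reproduce. The calculation below shows direction and plausible size only.

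**Input from the article.** The Background gives 84% progression within 15 years of seroconversion for children with multiple autoantibodies. Follow-up is 4 years.

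**Assumptions.** The hazard is constant and is applied from screening rather than from seroconversion. Uptake u, therapy hazard ratio HR and start time s (years after staging) are not in the article.

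**Untreated risk.** λ = −ln(1 − 0.84)/15 = 0.1222 per year. The 4-year risk is 1 − exp(−4 × 0.1222) = 38.7%.

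**Risk under the written rule.** (1 − u)[1 − exp(−4λ)] + u[1 − exp(−λs − λ·HR·(4 − s))].

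*Therapy from staging (s = 0), HR = 0.5.* The treated risk is 1 − exp(−4 × 0.1222 × 0.5) = 21.7%, which is 17.0 points below the untreated risk. The shortfall is u × 17.0 points:

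- u = 5%: 0.8 points (37.8%)
- u = 10%: 1.7 points (37.0%)
- u = 25%: 0.75 × 38.7% + 0.25 × 21.7% = 34.4%, a shortfall of 4.2 points
- u = 50%: 8.5 points (30.2%)

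*Therapy from 0.5 to 1 year, HR from 0.4 to 0.8:*

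| Uptake | 4-year risk under the rule | Shortfall (points) |
|---|---|---|
| 0% | 38.7% | 0 |
| 5% | 37.8–38.4% | 0.2–0.9 |
| 10% | 36.9–38.2% | 0.5–1.8 |
| 25% | 34.2–37.5% | 1.2–4.5 |
| 50% | 29.7–36.3% | 2.3–9.0 |

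**By stage.** A simulation of 400,000 children assumed 25% in stage 2, hazards of 0.30 (stage 2) and 0.09 (stage 1) per year, and therapy in stage 2 only, from 0.5 years. Uptake was 10–50% and HR 0.4–0.6.

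- The true untreated stage-2 risk was 69.7%. The written rule gave 56.6–68.2%.
- Censoring at therapy start within stage gave 69.6–69.9%. Therapy was allocated at random within stage, so this is the favourable case.
- Censoring at therapy start without separating the stages gave 36.6–39.6% against a true overall 40.2%. Censoring must therefore be done within initial stage.

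**Precision.** The target of 1300 children at 5–15% seropositivity gives 65–195 seropositive children, including single-antibody children who are not in stage 1 or 2. At a risk of 38.7%, the binomial 95% half-width is 1.96 × √(0.387 × 0.613/n), or about 12 points for n = 65 and 7 points for n = 195, before losses.

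**The case against.** The strongest reply is that therapy is not part of this study. The three phases consist of screening, education, staging and monitoring. The expectation of therapy stands in the Discussion, with no uptake or date and no statement that it will fall within this cohort's four years. The time rule is a conventional one-sentence summary, and handling of intercurrent treatment is often left to the analysis plan. The objective can also be read as descriptive tracking in a study about real-world implementation, where progression under actual care is a proper target. Finally, a bias of about 4 points lies inside the sampling error.

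Much of this stands:

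- A reader might infer that the estimate **is** too low. The article does not support that, because it does not establish that any child will be treated.
- A reader might also infer that the Cox model **will** understate the markers that make a child a therapy candidate. That requires therapy to be allocated by those markers, which no section says, and the open covariate list does not exclude a therapy term. Some distortion is possible; its direction and size are not shown.
- With so few children and perhaps only a handful of therapy starts, inverse-probability weights or a time-varying therapy term are not supportable as defaults.

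Two parts do not stand. The article is not merely silent, because it states an end-of-time rule and that rule absorbs treated time into an estimate meant to serve a natural-history objective. A shortfall smaller than the confidence interval is still systematic, and the interval does not warn of it.

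**Conclusion.** The point holds conditionally. As written, the rule estimates progression under screening and actual care, which equals natural history only if no child receives a therapy that changes progression. If some do, and the effect runs in the direction the Discussion gives, the estimate for the stages concerned lies below the untreated risk. That direction follows from the article's own text.

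The size rests wholly on assumed uptake, effect and timing, and on a constant hazard carried over from seroconversion to screening. At 5% uptake it is under 1 point in the scenarios tabulated; at 25% uptake with a hazard ratio of 0.5 from staging it is about 4 points; with no treated child it is zero. It could be larger within one stage if therapy is concentrated there. This is a modest and inexpensive correction to make before follow-up data accumulate. It takes no position on whether any child should be treated.

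**What to change.** 1. Record at the existing monitoring visits the start date of any disease-modifying therapy and of any entry into a prevention trial.
2. Keep the present Kaplan-Meier estimate, labelled as progression under screening and actual care.
3. If any child is treated, add a natural-history estimate by initial stage, with time censored at therapy start or prevention-trial entry, and report the number of such starts in each stage.
4. Repeat the Cox model with the same censoring as a sensitivity analysis.
5. Use weighting for that censoring only if the number of therapy starts can support it.

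The cost is one date field and one additional analysis. The natural-history estimate will have fewer events and wider intervals. It also assumes that, within initial stage, starting therapy is unrelated to a child's remaining risk. That assumption may fail if the children closest to onset are treated first, so it should be stated beside the result.

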### Statistical Analyses

#### Sample Size

The target enrollment is 1300 participants (or 322 families), based on the feasibility of recruiting 70% of eligible families from the UDC clinic cohort. The estimated seropositivity rate for islet autoantibodies among children with an FDR diagnosed with T1D is estimated at 5% to 15%, with a 90% significance level and 80% power. Considering that the UDC serves approximately 450-500 children with T1D, and that the typical Saudi family has 4-6 children younger than the age of 18 years, this sample size is calculated to be sufficient. Recruitment will be expanded to FDRs outside the UDC cohort if the family target is met without reaching the participant’s goal.

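### The sample size counts about four children per family, yet neither it nor the prevalence and progression analyses allow for within-family correlation

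*Protocol article*

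**What the plan says.** The Sample Size section of the protocol article builds its target from families: "The target enrollment is 1300 participants (or 322 families), based on the feasibility of recruiting 70% of eligible families from the UDC clinic cohort". It supports this with the clinic's size ("the UDC serves approximately 450-500 children with T1D") and with family size ("the typical Saudi family has 4-6 children younger than the age of 18 years"). It then gives an expected autoantibody rate of 5% to 15%, adds "with a 90% significance level and 80% power", and concludes that the number is sufficient. No design effect, within-family correlation or effective sample size appears.

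The prevalence of stages 1, 2 and 3 is a primary objective. For its analysis, the Statistical Analysis section says: "Feasibility metrics and T1D stages will also be summarized as percentages".

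Progression to stage 3 among presymptomatic participants is analysed by Kaplan-Meier, and "Cox proportional hazards models will assess factors associated with disease progression, such as baseline autoantibody titers, genetic risk scores, and demographic variables". The only methods named for correlated data, repeated-measures ANOVA and mixed effects models, are for psychological measures repeated over time. They do not address siblings.

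**The concern.** Siblings share genes, a household and the family's decision to take part. The article itself gives reasons to expect islet autoimmunity to cluster in families: its Background cites a 15-fold higher lifetime risk with an affected first-degree relative, and its HLA section attributes more than half of T1D heritability to that region. Four siblings therefore carry less information about prevalence than four unrelated children.

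If the family is ignored, a prevalence interval computed on 1300 children would be too narrow, and standard errors for progression would tend to be too small wherever siblings both enter. Prevalence is a primary objective, and the Conclusions of the abstract say the pilot is meant to inform a national screening programme, so its precision should be stated correctly.

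**Working it through.** **The plan's own figure.** The target follows from recruitment arithmetic. 70% of 450 to 500 is 315 to 350 families, and 70% of 460 is exactly 322. Then 322 × 4 = 1288, close to 1300. The mean family size is m = 1300/322 = 4.04.

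The stated significance level and power do not lead to 1300 as a test. Comparing 5% with 15% at α = 0.10 and 80% power needs 111 per group two-sided, or 81 one-sided. A 90% interval of ±1 percentage point at 5% prevalence needs 1286, but no such precision target is stated.

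**Prevalence.** The design effect is DEFF = 1 + (m − 1) × ICC = 1 + 3.04 × ICC. The effective n is 1300/DEFF, and the standard error grows by √DEFF. The documents give no ICC, so the values below are assumptions. The last two columns are for a prevalence of 10% and a 95% interval; the half-width that ignores families is 1.96 × √(0.10 × 0.90/1300) = 1.63 points.

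| ICC (assumed) | DEFF | Effective n | SE ratio | Correct half-width (points) | Coverage of an interval that ignores families |
|---|---|---|---|---|---|
| 0.01 | 1.03 | 1262 | 1.015 | 1.66 | 94.7% |
| 0.02 | 1.06 | 1226 | 1.03 | 1.68 | 94.3% |
| 0.05 | 1.15 | 1129 | 1.07 | 1.75 | 93.2% |
| 0.10 | 1.30 | 997 | 1.14 | 1.86 | 91.4% |
| 0.20 | 1.61 | 809 | 1.27 | 2.07 | 87.8% |

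**Which part of the range applies.** For a binary trait with prevalence p and sibling recurrence ratio RR, ICC = p(RR − 1)/(1 − p). RR is also an assumption, taken here as 2 to 3.

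- Any autoantibody, p = 5%, RR = 2: 0.05 × 1/0.95 = 0.053.
- Any autoantibody, p = 10%, RR = 3: 0.10 × 2/0.90 = 0.22.
- A single stage, p = 1% (assumed), RR = 2: 0.01 × 1/0.99 = 0.010, DEFF 1.03, intervals 1.5% wider.
- A single stage, p = 3% (assumed), RR = 3: 0.03 × 2/0.97 = 0.062, DEFF 1.19, intervals 9% wider.

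Stages 1 and 2 require two or more autoantibodies, so each is rarer than the 5% to 15% rate. For individual stages, the lower part of the table is the likelier one.

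**Progression.** Four per family does not apply here. At 5% to 15%, 65 to 195 of the 1300 children would carry any autoantibody, and fewer would carry two or more. A beta-binomial model with four children per family, p from 5% to 15% and ICC from near 0 to 0.30, gives about 1.1 to 1.7 positive children per affected family. The size-weighted mean w is 1.15 to 2.22.

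With a within-family correlation c of 0.1 to 0.3 (assumed), the SE ratio is √(1 + (w − 1)c):

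- low end: √(1 + 0.15 × 0.1) = 1.01;
- high end: √(1 + 1.22 × 0.3) = 1.17.

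This formula suits a covariate that is the same for all siblings. For one that differs between siblings, such as the child's own genetic score, the effect is smaller and its direction is not certain.

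**The case against.** The strongest reply is that the article is silent and does not commit an error. It names model types but no variance estimator. It is a condensed text, and a clustered variance within a named Cox model is commonly left to the analysis plan. That is right as far as it goes: a reader might infer that the plan analyses siblings as independent, but the article never says so. What remains is the sample-size statement, which is made in this document. It reaches its number by counting siblings and calls the result sufficient, with no allowance for their correlation.

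Other stronger readings also go beyond the text:

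- **That the planned prevalence intervals are too narrow.** The article plans percentages and describes no interval. Clustering leaves the percentage itself unchanged; the problem arises once precision is attached to it.
- **That the Cox model is the worst affected.** It covers presymptomatic children only, and most affected families contribute one. The covariates are given as demographic variables in general, so nothing shows that characteristics identical across siblings are meant.
- **That the paired tests treat children as independent.** Their subjects are caregivers, compared before and after, and nothing says a caregiver is entered once per child.
- **That 1300 came from a formula assuming independence.** The recruitment arithmetic explains the number, and the stated significance and power do not.

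It is also fair to say that the ICC is unknown, that all participants already have an affected relative, and that at an ICC of 0.01 to 0.02 the effect on prevalence is trivial.

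**Conclusion.** The point holds in moderate form. The target of 1300 children rests on about four per family, and neither the sample-size statement nor the prevalence and progression analyses mention within-family correlation. If children are treated as independent, the precision of the primary prevalence estimate is overstated. For an assumed ICC of 0.01 to 0.20, the effective sample size is about 1260 to 809 and intervals should be 1.5% to 27% wider, with individual stages more likely near the lower end. For Cox and Kaplan-Meier the effect is smaller, about 1% to 17% on the standard error.

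These figures assume equal family sizes of 4.04 and ICC values that are not in the documents. Unequal family sizes would raise the design effect somewhat. The family size itself is firm.

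**What to change.** - **Prevalence:** report each stage with a 95% confidence interval from GEE clustered on family, or from a bootstrap that resamples whole families.
- **Progression:** use a family-clustered robust variance for the Cox model and the Kaplan-Meier intervals. A shared-frailty Cox model is an alternative if there are enough events to support it.
- **Sample size:** restate the target as 1300 children in 322 families with its effective sample size over a range of ICC, for example 1262 at 0.01, 1129 at 0.05, 997 at 0.10 and 809 at 0.20, and the interval half-width that each implies.

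If the full protocol or analysis plan already specifies a clustered variance, only the sample-size statement needs changing. The fix needs the family link, which the study has because it enrols by family. Recruitment, visits and procedures stay as they are. The cost is slightly wider intervals.
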